## Abstract

**Background:**

Measles and oral polio vaccinations may reduce child mortality to an extent that cannot be explained by prevention of measles and polio infections; these vaccines seem to have beneficial non-specific effects. In the last decades, billions of children worldwide have received measles vaccine (MV) and oral polio vaccine (OPV) through campaigns. Meanwhile the under-five child mortality has declined. Past MV and OPV campaigns may have contributed to this decline, even in the absence of measles and polio infections. However, cessation of these campaigns, once their targeted infections are eradicated, may reverse the decline in the under-five child mortality. No randomized trial has assessed the real-life effect of either campaign on child mortality and morbidity. We present the research protocol of two concurrent trials: RECAMP-MV and RECAMP-OPV.

**Methods:**

Both trials are cluster-randomized trials among children registered in Bandim Health Project’s rural health and demographic surveillance system throughout Guinea-Bissau. RECAMP-MV is conducted among children aged 9–59 months and RECAMP-OPV is conducted among children aged 0–8 months. We randomized 222 geographical clusters to intervention or control clusters. In intervention clusters, children are offered MV or OPV (according to age at enrolment) and a health check-up. In control clusters, children are offered only a health check-up. Enrolments began in November 2016 (RECAMP-MV) and March 2017 (RECAMP-OPV). We plan 18,000 enrolments for RECAMP-MV with an average follow-up period of 18 months and 10,000 enrolments for RECAMP-OPV with an average follow-up period of 10 months. Data collection is ongoing. The primary outcome in both trials is non-accidental death or non-accidental first non-fatal hospitalization with overnight stay (composite outcome). Secondary outcomes are: non-accidental death, repeated non-fatal hospitalizations with overnight stay, cause-specific primary outcome, outpatient visit, and illness. We obtained ethical approval from Guinea-Bissau and consultative approval from Denmark.

**Discussion:**

Cluster randomization and minimum risk of loss to follow-up are strengths, and no placebo a limitation. Our trials challenge the understanding that MV and OPV only prevent measles and polio, and that once both infections are eradicated, campaigns with MV and OPV can be phased out without negative implications on child health and survival.

**Trial registration:**

NCT03460002.

## Background

The common public health understanding is that vaccines protect against their target infections and do little else. However, an increasing body of evidence challenges this understanding. Studies from low-income countries suggest that the live measles vaccine (MV) and the live oral polio vaccine (OPV) reduce the under-five child mortality to an extent that cannot be explained by prevention of measles or polio infections; both vaccines seem to have what is termed beneficial non-specific effects (NSEs) [1]. In a systematic review commissioned by the World Health Organization’s (WHO) Strategic Advisory Group of Experts on Immunizations (SAGE) it was concluded in 2014 that, “There was consistent evidence of a beneficial effect of measles vaccine (…)” on child mortality. This conclusion was based on four randomized trials and 18 observational studies [2] but SAGE called for more research [3]. Though the effect of OPV was not included in the review, OPV also seems to have beneficial NSEs: In two trials, where infants were randomised to OPV or no OPV at birth, OPV was associated with a 32% lower infant mortality in both trials [4, 5]. Observational studies also indicate that children receiving OPV with a non-live vaccine have better survival than children receiving the non-live vaccine only [6, 7]. We respond to SAGE’s call for more research by assessing the NSEs of an MV campaign and an OPV campaign.

In the last decades, billions of children have received MV and OPV through campaigns implemented worldwide with the goal to ultimately eradicate measles and polio infections [8, 9]. The campaigns aim at reaching all children in a broad age-group regardless of pre-campaign vaccination status, also children who are not reached through routine vaccination program services. The campaigns can increase population immunity against the viruses rapidly, thereby interrupting virus transmission, which leads to herd protection [10, 11]. The under-five child mortality has declined on a global scale [12] in the same period as campaigns with MV and OPV have been conducted. Thus, we suggest that past MV and OPV campaigns may have efficiently contributed to reduce the under-five child mortality given their presumed beneficial NSEs, even in the absence of measles and polio infections. Cessation of MV and OPV campaigns after eradication of their targeted infections may therefore reverse the declining trend in the under-five child mortality.

No randomized trial has assessed the real-life effect of an MV campaign or an OPV campaign on child mortality. Two observational studies were published after WHO’s SAGE review, and both support that MV campaigns among children reduced the under-five mortality. In a before/after study among 8000 children, mortality in the year following an MV campaign was 20% (4–34%) lower compared with the year prior to the campaign, even after censoring measles deaths (17% (0–31%)) [13]. Another study compared mortality in MV campaign participants (5633) with non-participants (1006) in the year following the campaign, and mortality was found to be 72% (23–90%) lower among participants; no deaths were measles related [14]. In both studies, children who were also measles vaccinated through routine vaccination program services seemed to additionally benefit from the MV campaign [13, 14]. Similarly, OPV campaigns may reduce child mortality considerably. Among children followed in seven trials of vaccines or vitamin A supplements, an OPV campaign was associated with a 19% (5–32%) lower mortality rate [15]. Comparisons of mortality after OPV campaigns with mortality before the campaigns in other cohorts also indicated lower mortality for children exposed to OPV campaigns [16, 17], and adjusted for age, receiving OPV in a campaign was associated with a 91% (20–99%) lower mortality than not receiving OPV in a campaign [18].

In two concurrent cluster-randomized controlled trials, we want to assess the separate effect of an MV campaign and an OPV campaign on child health and survival in the absence of measles and polio infections. We present the research protocol of each trial: Real-life Effect of a CAMPaign with a Measles Vaccination (RECAMP-MV) and Real-life Effect of a CAMPaign with an Oral Polio Vaccination (RECAMP-OPV). We initiated enrolments into RECAMP-MV in November 2016 and will conduct follow-up until eligibility for a national measles vaccination campaign (trial completion is expected by late 2019). We initiated enrolments into RECAMP-OPV in March 2017 and will conduct follow-up until eligibility for any national vaccination campaign or a maximum of 12 months (trial completion is expected by late 2020). A data safety and monitoring board consisting of a statistician, a pediatrician, and an epidemiologist is providing input to ensure an optimal data collection process.

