### Design and randomization

The 222 village clusters were randomized to intervention or control clusters stratified by region and access to health services. We defined health service access as vaccination coverage by 12 months of age assessed among children aged 12–23 months [24], using BHP HDSS data from 2015 to 2016. This pre-trial vaccination coverage was based on Bacillus Calmette Guerin (BCG) vaccine, three doses of OPV, three doses of Pentavalent (diphtheria, tetanus, pertussis, hepatitis B, haemophilus influenza type B), and MV. We defined low and high pre-trial vaccination coverage using the median as a cut-off point. Within each of the two coverage strata per region, we assigned one half of the clusters to receive intervention and health check-up, and the other half to receive only health check-up, based on an externally generated random number.

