After consent, the enrolling nurse performs a health check-up of one child at a time (assessing illness, issues with prior vaccination, and measuring axillary temperature, mid-upper-arm-circumference, and weight). If the enrolling nurse experiences that a child is overtly ill, the child’s mother/guardian is given health advice, and if necessary offered health facility transport, irrespective of cluster assignment. Overtly ill children are offered enrolment at a subsequent visit, if recovered.

If a child is assessed healthy in intervention clusters, the child aged 9–59 months is administered a 0.5 ml reconstituted MV from a 10-dose vial by deep subcutaneous injection into the left subscapular region (leftover doses are discarded six hours after reconstitution), and the child aged 0–8 months is administered two oral drops of OPV from a multi-dose vial (leftover doses are discarded after 28 days). If a child is assessed healthy in control clusters, the child is not administered MV or OPV.

All enrolled children are followed through regular household visits by field assistants who collect information on death and hospitalization, among other. The visits are conducted every two months to children < 12 months of age in Oio, Biombo and Cacheu for logistical reasons, and every six months to older children, and in the remaining regions. If a field assistant registers the death of a child, a specially trained field assistant conducts a verbal autopsy at a subsequent visit [28]. An extra follow-up visit is conducted among a subgroup of enrolled children one-two months after enrolment; the mothers/guardians of these children are visited by field assistants to collect information on outpatient visit and maternally reported illness in the elapsed time span. This visit is also utilized to provide a second OPV dose to children aged 0–8 months in intervention clusters. Figure 2 shows the flow from eligibility to follow-up in RECAMP-MV and RECAMP-OPV.

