#### Sensitivity analyses of primary outcome

We will assess the robustness of the primary analysis of the primary outcome for each campaign under different scenarios:
two intention-to-treat analyses: 1) in a classic intention-to-treat analysis children will be included if present in the cluster from the day they were first potentially eligible to enter but did not because they e.g. did not receive the assigned treatment, were excluded due to illness, did not have a mother/guardian to escort them, or had a mother/guardian who refused participation, 2) in an extended intention-to-treat analysis children will be included if living in the cluster from the day they were first potentially eligible to enter (including children from the classic intention-to-treat analysis and children who were absent/travelling) as either campaign may affect other children’s health in the community by reducing the general infectious pressure.Furthermore, we will assess if different censoring criteria affect the robustness of the results

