## Discussion

This paper presents the methodology of two concurrent cluster randomized controlled trials named RECAMP-MV and RECAMP-OPV. We will assess the real-life effect of an MV campaign among children aged 9–59 months (RECAMP-MV) and the real-life effect of an OPV campaign among children aged 0–8 months (RECAMP-OPV) on non-accidental mortality or non-accidental morbidity (composite outcome) in rural Guinea-Bissau**,** where measles infection is limited and no polio circulates. Major strengths lie within the cluster randomisation design which allows us to assess each campaign’s effect on the general infectious pressure, which would not be possible with individual randomisation. Furthermore, the BHP’s rural HDSS ensures a reliable and thoroughly tested data collection and data management infrastructure minimizing the risk of loss to follow-up. In the following, we consider a major limitation, circumstantial challenges, and future perspectives.

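### MV and OPV share one two-arm randomisation, so community effects belong to the combined campaign, and separate vaccine effects need an unstated assumption of no spillover between age groups

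*Protocol article*

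**What the plan says.** **Allocation.** The abstract reports a single randomisation: "We randomized 222 geographical clusters to intervention or control clusters". The section Design and randomization confirms two arms: "we assigned one half of the clusters to receive intervention and health check-up, and the other half to receive only health check-up".

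**What an intervention cluster receives.** From the abstract: "In intervention clusters, children are offered MV or OPV (according to age at enrolment) and a health check-up". Under Enrolment and follow-up procedures, "If a child is assessed healthy in intervention clusters, the child aged 9–59 months is administered a 0.5 ml reconstituted MV", and the same sentence goes on to give OPV drops to those aged 0–8 months. Healthy children in control clusters receive neither vaccine.

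**What is claimed.** The Background says "we want to assess the separate effect of an MV campaign and an OPV campaign on child health and survival". The Objectives set one age-specific aim per trial. The Discussion says that cluster randomisation "allows us to assess each campaign’s effect on the general infectious pressure". Its closing paragraph draws implications for MV and for OPV vaccine by vaccine.

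**Spillover.** The extended intention-to-treat analysis adds absent and travelling children, "as either campaign may affect other children’s health in the community by reducing the general infectious pressure".

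**What separates the trials.** Under Study population, a child enrolled in RECAMP-OPV is not later enrolled in RECAMP-MV. Each enrolled child is thus in one trial and is offered one trial vaccine. The limitations in the Discussion do not mention that the two allocations coincide.

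**The concern.** An infant in an intervention cluster is offered OPV and also lives among older children who were offered MV. An infant in a control cluster has neither exposure. RECAMP-MV is the mirror image. If vaccinating one age group changes infection risk in the other, each trial's hazard ratio mixes its own campaign's effect with an indirect effect of the other campaign. For community effects there is not even a direct component to set the two apart: a child who was never enrolled lives in a village with both campaigns or with neither.

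What is at stake is attribution. The article wants to say what would be lost if MV campaigns, or OPV campaigns, were phased out. A benefit seen in infants could in part be owed to MV in older children, and the reverse. The randomised comparison and the power are not in question.

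**Working it through.** **1. Reproduce the stated power, to show that the issue lies elsewhere.** Inputs from Sample size considerations, Table 2 and its footnotes: 222 clusters, so c = 111 per arm; coefficient of variation k = 0.25; alpha 0.05, taken as two-sided; harmonic mean person-years per cluster y = 84 (MV) and 40 (OPV); control rates λ0 = 0.017 and 0.055 per person-year; reductions of 30% and 25%.

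Hayes–Moulton formula for rates in unmatched clusters, solved for power:

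power = Φ( √[(c − 1)(λ0 − λ1)² / V] − 1.96 ), with V = (λ0 + λ1)/y + k²(λ0² + λ1²)

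- MV, λ1 = 0.0119: V = 0.0289/84 + 0.0625 × 0.00043061 = 0.00037096. √(110 × 0.0051² / V) = 2.777. Power = Φ(0.817) = 79.3%.
- OPV, λ1 = 0.04125: V = 0.09625/40 + 0.0625 × 0.00472656 = 0.0027017. √(110 × 0.01375² / V) = 2.774. Power = Φ(0.814) = 79.2%.

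With the rounded rates in the footnotes (17 versus 12, and 55 versus 41) the results are 77.6% and 80.8%. The stated 80% is reproduced in substance.

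**2. Set out the exposures.**

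| Arm | Age 0–8 months | Age 9–59 months |
|---|---|---|
| Intervention | OPV offered; MV given around them | MV offered; OPV given around them |
| Control | neither | neither |

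There is no MV-only or OPV-only row. Between arms, on the rate-ratio scale:

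RR(OPV trial) = RR(own OPV campaign) × RR(spillover from MV)

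RR(MV trial) = RR(own MV campaign) × RR(spillover from OPV)

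One contrast per age group cannot yield two factors. The first factor is recovered only if the second is fixed, and setting it to 1 is the assumption of no cross-age spillover. In a child who was not vaccinated by either trial, all that can be estimated is the joint community effect.

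**3. Show how far attribution could move.** The documents give no spillover size, so the ratios s below are assumptions. The implied own-campaign ratio is the observed ratio divided by s, with the planned effects (0.75 and 0.70) taken as observed. The probability of a significant benefit when the own campaign does nothing comes from the formula above with λ1 = s × λ0. Example, OPV with s = 0.90: λ1 = 0.0495, V = 0.0029547, √(110 × 0.0055² / V) = 1.061, Φ(1.061 − 1.96) = 18.4%.

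| Assumed s | OPV: own RR if 0.75 observed | OPV: chance of significant benefit, own RR = 1 | MV: own RR if 0.70 observed | MV: chance of significant benefit, own RR = 1 |
|---|---|---|---|---|
| 0.95 | 0.79 | 7.5% | 0.74 | 6.3% |
| 0.90 | 0.83 | 18.4% | 0.78 | 13.9% |
| 0.85 | 0.88 | 36.5% | 0.82 | 26.4% |
| 0.80 | 0.94 | 58.9% | 0.88 | 43.5% |

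With s = 1 the chance of a significant benefit is the nominal 2.5% and the own-campaign ratio equals the observed one.

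**The case against.** The strongest reply is that the aims are age-specific. Each enrolled child is in one trial, is offered one trial vaccine, and is compared with control children of the same age in a per-protocol Cox model. On this reading, a separate effect means one estimate per trial and age group, and the design delivers that. This largely stands. A reader might infer that the plan cannot estimate separate effects at all. The documents do not support that, because each contrast isolates its own campaign if there is no cross-age spillover.

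A reader might also say that the article flatly contradicts itself. That goes too far. The sensitivity-analysis section says only that a campaign may affect other children, and spillover within one trial's own age group would be enough to justify the extended analysis. Spillover between age groups is neither stated nor excluded. Nor does the article give infectious pressure as its reason for randomising clusters; the Discussion lists it as a strength. The result is a tension with an unstated assumption.

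Nor is it right that the data hold no information on separate indirect effects. MV enrolment began in November 2016 and OPV enrolment in March 2017, with completion expected in late 2019 and late 2020. After a national MV campaign, older control children would also be eligible for MV, so infants enrolled later would have a weaker MV contrast around them. But the first months were a pilot phase in one region, and the number of later infants is not given. The information is partial and of unknown amount.

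Finally, a reader might object that the two trials are not independent replications. That is true, but the article makes no such claim. The spillover ratios in the table have no support in the documents and show sensitivity only.

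None of this rescues the Discussion's statement about infectious pressure.

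**Conclusion.** The point holds in two parts of different strength.

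First, the Discussion claims a property that the design lacks. With one two-arm allocation of 222 clusters, any effect on general infectious pressure, including one seen in the extended intention-to-treat analysis, belongs to the combined MV and OPV village campaign. This rests on the allocation alone and needs no assumed figure.

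Second, reading each trial's result as the effect of one campaign needs the assumption of no spillover between infants and older children. The article does not state it, and its own argument about infectious pressure makes it hard to take for granted. How much this matters depends on a quantity that the documents do not give: under the assumed ratios of 0.95 to 0.80, it runs from slight to most of the planned effect.

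The age-specific contrasts, the power and the randomised comparison of the combined campaign with check-up only are unaffected.

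**What to change.** - In the Discussion, reword the strength: cluster randomisation allows assessment of the combined campaign's effect on infectious pressure. Interpret the extended intention-to-treat analysis in the same way.
- Beside the aim in the Background, the primary objectives, and the vaccine-specific conclusions that close the Discussion, state that attribution to one campaign assumes no spillover between the 0–8 and 9–59 month groups.
- Add the coinciding allocation to the limitations.

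A subgroup analysis by whether a child eligible for the other trial lives in the same household may suggest itself. It should be left out, or labelled exploratory. A child with no such housemate still lives in a village with both campaigns, so a null result would not exclude village-level spillover. Household composition is also not randomised, so a difference would be open to other explanations. Separate indirect effects would need factorial or separately randomised clusters, which enrolled clusters cannot supply.

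The cost is a few sentences, with no change to data collection or to the primary model. The downside is a narrower claim.

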### Objectives

#### Primary objectives

RECAMP-MV: To assess the real-life effect of an MV campaign among children aged 9–59 months on non-accidental mortality or non-accidental morbidity (composite outcome) in rural Guinea-Bissau, where measles infection is limited. We will test whether an MV campaign can reduce the composite outcome by 30% during an average follow-up period of 18 months.

RECAMP-OPV: To assess the real-life effect of an OPV campaign among children aged 0–8 months on non-accidental mortality or non-accidental morbidity (composite outcome) in rural Guinea-Bissau, where no polio circulates. We will test whether an OPV campaign can reduce the composite outcome by 25% during an average follow-up period of 10 months.

#### Secondary objectives

To better understand the real-life effect of either campaign on child health and survival we will also assess the effect of each campaign on other health measures and under different scenarios as specified in the statistical analysis section.

## Methods/design

### Setting

Guinea-Bissau’s Ministry of Health has implemented national MV campaigns among children aged 9–59 months every third year since 2006 [19], and OPV campaigns more frequently [15]. Despite some fluctuations in reported measles infection cases [20] and MV coverage [21], Guinea-Bissau has a low risk profile of measles (Table 1) and the last recorded case of indigenous wild poliovirus in Guinea-Bissau was in 1999 [22].

**Table 1 Tab1:** Measles infection cases, vaccination coverage and vaccination campaigns in Guinea-Bissau according to WHO’s country data [20, 21]

*Year*	2008	2009*	2010	2011	2012*	2013	2014	2015*	2016	2017
Measles infection cases (number)	12	0	26	0	0	0	1	153	0	11
1st routine measles dose (proportion)	64%	79%	78%	78%	90%	89%	81%	90%	71%	66%

*****Guinea-Bissau’s Ministry of Health implemented a national measles vaccination campaign

*Abbreviation*: WHO=World Health Organization

Bandim Health Project (BHP) follows women of fertile age and children under-five in Guinea-Bissau’s rural population through a health and demographic surveillance system (HDSS). This enables assessment of child mortality and morbidity. In Guinea-Bissau’s nine rural health regions (Oio, Biombo, Gabu, Cacheu, Bafata, Quinara, Tombali, Bubaque, and Bolama), 222 randomly selected geographical clusters with more than 22,000 children under-five are being monitored. The selection process of the geographical clusters has been described elsewhere [23]. Field teams conduct regular visits to all villages in all clusters. At household visits field assistants register pregnancies, and children’s vaccination status, mortality, morbidity, nutritional status, campaigns with other health interventions, migration, and whereabouts if absent [23]. This is the implementation platform of RECAMP-MV and RECAMP-OPV.

